#### Sustainability

Perceptions of sustainability will be evaluated through semistructured individual interviews with consumers and clinicians. These qualitative descriptive interviews will explore user experiences, perceived barriers and enablers to continued use, and suggestions for long-term implementation and integration into clinical workflows.

#### Preliminary Effectiveness

The secondary outcomes are included to explore early signals of the intervention’s potential effectiveness and to inform future trial design. These outcomes include changes in consumer activation, self-rated health, and calculated disease risk scores. Consumer activation will be assessed using the 10-item Consumer Health Activation Index (CHAI), a validated measure of an individual’s knowledge, skills, and confidence in managing their health [96]. CHAI has demonstrated high internal reliability and predictive validity for health behavior change [27,96,103]. Self-rated health will be measured via a single-item rated on a 5-point Likert scale, which is widely used as a proxy for general health status [104]. Chronic condition risk scores will be calculated from data within the THRIVE platform at baseline and at 6 months postenrollment.

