## Introduction

### Background and Rationale

Chronic conditions, including cardiovascular disease, type 2 diabetes, and common cancers, contribute to a substantial and growing global health and economic burden [1-3]. These conditions arise from complex interactions between modifiable (eg, smoking, inactivity, and poor diet) and nonmodifiable (eg, age, ethnicity, and family history) risk factors [4]. Importantly, over 17 million premature deaths each year are attributable to preventable causes [1,2], highlighting the critical role of primary and secondary prevention in reducing disease burden and improving population health outcomes.

While the cost-effectiveness and long-term benefits of prevention are well established, many health systems continue to struggle to deliver equitable, timely, and comprehensive preventive care—particularly within general practice [5-7]. General practice serves as the frontline of health care, encompassing health promotion, early detection and intervention, and the management of acute and chronic conditions [8]. In Australia, despite national policy commitments to preventive health [9]; systemic barriers, such as fragmented services and inadequate financial incentives for preventive activities; and chronic underinvestment in general practice continue to impede the implementation of effective prevention models [10-13].

Participation in preventive services remains suboptimal in Australia, with only 52% of eligible women participating in breast cancer screening [14] and only 42% of eligible adults undertaking bowel cancer screening [15]. Routine recording of risk factor data for common chronic conditions, such as cardiovascular disease and type 2 diabetes, is also inconsistent. This limits the feasibility of proactive risk identification, with data recorded for only 49% and 24% of the population, respectively [16,17]. These gaps underscore the need for scalable, system-wide strategies to increase access to and engagement with preventive care. Digital health interventions (DHIs) are a promising avenue to strengthen preventive care delivery, yet their acceptability, engagement, and feasibility in real-world general practice settings remain underexplored.

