### Participants

#### Consumer Sampling and Recruitment

A convenience sample of consumers will be recruited from participating practices. Eligible consumers will be adults aged 30 to 65 years, who can speak English and have regular access to an internet-enabled digital device, such as a smartphone, tablet, or computer. This age range was selected to maximize preventive potential, targeting individuals most likely to benefit from lifestyle changes and screening engagement before the onset of chronic conditions.

Each practice will recruit consumer participants over a 3-month recruitment period. The recruitment process will be multifaceted. Primarily, brochures or posters with QR codes will be displayed in waiting and consulting rooms, allowing individuals to access information via their mobile phones while they are waiting. This QR code links to a webpage where people can register their interest, receive study information, and complete the consent form. Additionally, study information will be disseminated via practice newsletters and/or emails if available. To minimize burden on the participating practices, clinicians are not expected to recruit consumers; however, individual clinicians can opportunistically encourage consumers to consider participation.

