THRIVE generates personalized lifetime chronic condition risk estimates using a composite lifetime modeling framework. This model synthesizes demographic variables, behavioral risk factors, family history, anthropometric measures, and selected clinical data based on evidence from Australian and international epidemiological studies. Inputs and effect sizes are derived from hazard ratios, attributable risk fractions, and pooled effect estimates from meta-analyses and high-quality cohort data. Construct validation has been undertaken for risk estimates that have existing short-term (typically 5-year-risk) calculators by benchmarking THRIVE-generated risk scores against these tools, including the Australian Type 2 Diabetes Risk Assessment Tool [70], the Australian Cardiovascular Risk Score [71], and STOP-BANG for sleep apnea [92]. Validation analyses demonstrated moderate (STOP-BANG) to near-perfect (Australian Type 2 Diabetes Risk Assessment Tool) construct alignment with these established tools, and all recommendations are consistent with Australian clinical guidelines [66-69] (Multimedia Appendix 1 [66,68-91]).

Findings from this study, including quantitative engagement metrics and qualitative acceptability data, will inform subsequent model refinement to enhance usability in practice, ensure clinical appropriateness, and integrate into clinical workflows before a future large-scale trial.

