#### Intervention Content and User Experience

THRIVE guides users through lifetime chronic condition risk assessments, facilitates goal setting, and tracks and reinforces progress through behavioral “nudges.” The intervention is largely automated and can be used independently by consumers. Once consumer participants have provided consent and completed the preintervention survey, they receive a personalized email link providing access to the THRIVE platform. The online assessment guides users through a dynamic, user-friendly series of questions tailored to individual responses. Questions incorporate 130 validated risk and protective factors, and participants receive real-time feedback to maintain motivation and minimize attrition.

After completing the assessment, participants access a personalized dashboard that presents lifetime risk estimates for 23 chronic conditions, including cardiovascular disease, metabolic conditions, osteoporosis, sleep apnea, various cancers, eye and kidney disease, and an estimated “medical age.” The medical age score reflects the impact of lifestyle choices on microlife calculations (a microlife is a statistical unit representing 30 minutes of life expectancy gained or lost due to daily habits). Color-coded indicators highlight key contributors to risk. These risk estimates and the medical age-metric personalize lifetime risk estimates. Risk estimates and the “medical age” metric are not diagnostic tools and are intended solely for promoting health education and engagement. Multimedia Appendix 1 [66,68-91] provides a summary of all variables included in THRIVE’s risk-modeling framework, as well as the guideline sources informing action-plan content.

The platform translates risk estimates into actionable guidance using rule-based logic aligned with Australian clinical guidelines [66-69]. After viewing their dashboard, participants can access an automated action plan that provides tailored lifestyle and medical screening recommendations aligned with current Australian guidelines. Recommendations are presented using nudge-informed design principles that simplify decision-making while preserving user autonomy.

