Consumers can also access a clinician report that consolidates risk estimates, key health indicators, and recommendations, which they can choose to share with their general practitioner or general practice nurse to facilitate preventive-care discussions. This report also identifies Medicare Benefits Schedule items that the consumer may be eligible to receive to promote access to care. However, clinicians retain full discretion regarding consumer eligibility and the appropriateness of any care activity and associated Medicare Benefits Schedule claims.

Consumers are encouraged to set health goals and may choose to integrate data from wearable devices. They can also complete a quarterly “pulse check,” a brief reassessment that updates their health data, provides refreshed risk calculations, and tailors action plans. To support ongoing engagement, participants retain continuous access to their dashboard and can revisit it at any time to review progress or modify goals. Optional behavioral prompts and reminders are delivered to further support sustained use. Figure 1 illustrates the THRIVE dashboard and platform overview.

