### Outcomes

#### Overview of Outcome Measures

The primary focus of this study is feasibility, which will be assessed through consumer and clinician engagement, acceptability, and perceived sustainability (Table 1). A secondary outcome is preliminary effectiveness, evaluated through changes in consumer activation, self-rated health, and disease risk scores.

**Table 1. T1:** Overview of outcome measures.

Outcome and components	Data collection tool	Participants	Collection timeframe
Primary outcome (feasibility)			
Engagement	Usage logs from THRIVE platform	Consumers	Observation period
Acceptability	UTAUT2^a^ survey questions [93-95]	Consumers and clinicians	Postintervention
Sustainability	Semistructured interviews	Consumers and clinicians	Postintervention
Secondary outcomes (effectiveness)			
Consumer activation	CHAI^b^ survey questions [96]	Consumers	Preintervention and postintervention
Self-rated health	Single-item Likert Scale survey question	Consumers	Preintervention and postintervention
Calculated disease risk scores	AUSDRISK^c^ [70] and AusCVDRisk^d^ [71] scores calculated from THRIVE data	Consumers	Observation period

a UTAUT2: extended unified theory of acceptance and use of technology 2.

b CHAI: Consumer Health Activation Index.

c AUSDRISK: The Australian Diabetes Risk Score.

d AusCVDRisk: The Australian Cardiovascular Disease Risk Score.

The consumer baseline survey will also capture factors that may influence engagement with the intervention, including sociodemographic characteristics, perceived disease threat, and trust in the therapeutic relationship. Perceived disease threat will be measured using 4 validated items from the UTAUT2 framework [93], rated on a 7-point Likert scale ranging from “strongly disagree” to “strongly agree” (⍺=0.817). Trust in the therapeutic relationship will be assessed using the Trust in Physician Short-Form Scale [97]. These baseline variables will form the a priori covariate set for exploratory quantitative analyses examining predictors of engagement with the THRIVE intervention and potential signals of change in secondary outcomes. They will also be used to inform question refinement for the postintervention interviews, ensuring representation of diverse experiences and perspectives across engagement levels.

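### The 6-month change in the diabetes and cardiovascular risk scores can mix new measurement with changed risk, and people who already have the disease may be scored

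*Protocol article*

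**What the plan says.** Under Preliminary Effectiveness the protocol article lists the secondary outcomes: "These outcomes include changes in consumer activation, self-rated health, and calculated disease risk scores". It then fixes the source and timing: "Chronic condition risk scores will be calculated from data within the THRIVE platform at baseline and at 6 months postenrollment". Table 1 (Overview of Outcome Measures) names AUSDRISK and AusCVDRisk, describes them as "scores calculated from THRIVE data", assigns them to consumers and gives the timing only as the observation period.

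Intervention Content and User Experience describes a baseline assessment covering 130 factors. After it, "participants can access an automated action plan that provides tailored lifestyle and medical screening recommendations". The same section offers an optional quarterly pulse check, a short reassessment that refreshes the stored health data and the risk calculations.

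Consumer Sampling and Recruitment explains the age range as "targeting individuals most likely to benefit from lifestyle changes and screening engagement before the onset of chronic conditions". The eligibility conditions themselves are age 30 to 65, ability to speak English and regular access to a connected device.

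Secondary Outcome Analyses calls these analyses exploratory and non-causal, lists age among the covariates, and says the results will help choose outcomes and plan the sample size of a later effectiveness trial.

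**The concern.** A change score is informative about risk only if the two calculations differ because the person's risk differs. Here the intervention can alter what is measured. A participant who follows a screening recommendation may enter a clinical value that was unknown at baseline. If that value is high, the second score rises although risk is the same and the intervention did what it was meant to do; if it is favourable, the score may fall for an equally artificial reason. Because the mechanism runs through use of the platform, it would be concentrated in the more engaged participants.

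The scores are also meant to express the risk of developing a disease. In someone who already has it, a change in that score has no clear meaning, and the stated entry conditions let such people in.

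What is at stake is the planning of the next trial. A contaminated mean change could lead to the wrong outcome being chosen, and a contaminated spread would feed into its sample size.

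**Working it through.** The article gives no expected change, standard deviation or power for the risk scores, so there is no stated figure to reproduce. The check compares what the sections say and then sizes the parts that can be sized under labelled assumptions.

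1. **Are the two calculations like for like?** The baseline source is the full assessment covering 130 factors. The only later platform reassessment described is the pulse check, which is optional and short. No section says that both scores use the same inputs, or how a value absent at baseline but present at 6 months is treated. The same platform recommends screening between the two dates. New measurement can therefore enter the difference.

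2. **Who is scored?** The age-range rationale points to people before disease onset, but that is a reason and not a criterion. No exclusion for diagnosed diabetes or cardiovascular disease is given, and no restriction of the risk-score analysis by baseline diagnosis. Recruitment is mainly through waiting and consulting rooms, where such patients are likely to be present.

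3. **Ageing.** The introduction lists age among the "nonmodifiable (eg, age, ethnicity, and family history) risk factors". Everyone is 0.5 years older at the second calculation. If a score uses age bands of width w years and ages are spread evenly (both assumptions), the share crossing a band is 0.5/w:
   - w = 1 (completed years): 0.5/1 = 50%, about 108 of 215
   - w = 5: 0.5/5 = 10%, about 22 of 215
   - w = 10: 0.5/10 = 5%, about 11 of 215

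   These counts use the full target of 215. At the article's planning value of 50% completing the assessment, only about 215 × 0.5 = 107.5 would have a baseline score, and the counts halve. If instead absolute risk doubles every 8 to 10 years of age (assumption), the relative rise in 6 months is 2^(0.5/10) = 1.035 to 2^(0.5/8) = 1.044, that is 3.5% to 4.4%.

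   The age covariate does not remove this. It adjusts for differences between people of different ages, while the drift happens within each person.

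4. **Effect of newly entered inputs on the mean and spread.** Suppose a share s of participants has a score that moves by d units for reasons other than changed risk. The mean change shifts by s × d. If these shifts are independent of true change, they add s(1 − s)d² to the variance. Illustrative values, since the documents give neither s nor d:
   - s = 5%, d = 1: mean shift 0.05 × 1 = 0.05; added variance 0.05 × 0.95 × 1 = 0.0475
   - s = 30%, d = 3: mean shift 0.30 × 3 = 0.9; added variance 0.30 × 0.70 × 9 = 1.89

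   The range is wide, so the article alone cannot say whether the distortion is trivial or material.

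**The case against.** The strongest reply is that this is silence and not error. A journal article commonly leaves the computation of a derived score to the analysis plan, and this one promises a plan that is reviewed and preregistered before data extraction. The outcome is secondary, the analysis is declared exploratory and non-causal, and the Progression Criteria rest on engagement, acceptability and qualitative findings. Holding age fixed and dropping inputs also departs from the instruments as designed, so an as-recorded score is a defensible choice.

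Much of this stands and limits the weight of the point. It does not dispose of it: the outcome definition and the entry conditions are set in this article, and followed as written they yield a difference that can mix measurement with risk. Disclaiming causality does not change what is measured.

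Several stronger readings are tempting but not supported:
- A reader might infer that wearable data move these scores, because "Consumers are encouraged to set health goals and may choose to integrate data from wearable devices". No section says that wearable data enter AUSDRISK or AusCVDRisk. The stated inputs ("This model synthesizes demographic variables, behavioral risk factors, family history, anthropometric measures, and selected clinical data") describe THRIVE's separate lifetime model.
- A reader might infer that people with existing disease are scored. The text only fails to exclude them, so they may be scored. The consumer entry in Table 1 separates consumers from clinicians and does not define an analysis set.
- A reader might take the introduction's 49% and 24% of the population with recorded risk-factor data and conclude that 51% and 76% of participants (100 − 49 and 100 − 24) lack inputs at baseline. Those figures concern routine recording, not answers to a guided assessment, and nothing links the two.
- A reader might liken the ageing drift to the effect of a lifestyle change. The documents give no such effect to compare it with.
- A reader might fear that ageing creates a false signal of benefit. If the scores rise with age, it works against apparent improvement.

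**Conclusion.** The point holds as a minor one. As defined, the change in AUSDRISK and AusCVDRisk need not reflect changed risk. The main reason is that inputs can first appear after baseline, prompted by the intervention itself. The second is that people who already have the condition may be included. Ageing is a small third component: 5% to 10% of participants crossing an assumed 10- or 5-year band, or a 3.5% to 4.4% relative rise under an assumed doubling time.

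The overall size is unknown, because the documents give neither the share of participants with new inputs nor the score distributions. The conclusion assumes that the two scores use at least one clinical value a participant may lack at baseline and, for the drift, that they rise with age. The text shown does not list their inputs, and the unseen analysis plan may settle some of this. The practical relevance lies in the planned use of these results for the later trial, not in any decision within this study.

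**What to change.** Add to Preliminary Effectiveness or Secondary Outcome Analyses, and carry into the analysis plan before it is registered:

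- The change in each score is computed in participants without that condition at baseline, where THRIVE or the baseline survey records it.
- Both calculations use the same set of inputs, with age held at its baseline value.
- Clinical values first entered after baseline are left out of the change and reported separately as screening uptake.
- The as-recorded score is kept as a descriptive addition.

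This changes analysis wording only, and affected participants stay in the study for all other outcomes. The cost is that fewer participants and inputs contribute to the change score. The sponsor should first confirm that baseline diagnoses are recorded, since no section shows that they are. If they are not, the first rule cannot be applied to those already enrolled without collecting that item, and the limitation should be stated.

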#### Progression Criteria

Consistent with contemporary guidance for feasibility studies of complex and digital health interventions, such as the UK MRC framework [48], a flexible progression framework will be used rather than a binary go or no-go decision. Feasibility outcomes (engagement and acceptability) will be interpreted alongside qualitative findings to guide iterative refinement of the intervention prior to a future effectiveness trial.

A 3-level progression approach will be applied as follows:

Proceed: primary feasibility indicators meet predefined thresholds, and qualitative data suggest overall acceptability and workflow fit.Proceed with modifications (expected primary pathway): one or more indicators fall below the threshold, or qualitative findings identify modifiable barriers. Findings will inform targeted refinements to the intervention, implementation strategies, or study procedures before advancing to a powered trial.Do not proceed without redesign: multiple feasibility indicators fall below the threshold, and qualitative data indicate fundamental concerns that cannot be addressed through minor modifications.

This approach is consistent with the study’s purpose—to inform iterative refinement and future trial design rather than to provide definitive go or no-go criteria.

### Data Management

The THRIVE dashboard and clinician summary report are visible only to the consumer participant through their secure, personalized link. No identifiable or dashboard data are shared with clinicians or transferred to general practice systems. Only the consumer participant can choose to share their outputs or the clinician report.

Identifiable consumer participant information (first name and email address) will be collected solely to link preintervention and postintervention data. These identifiers will be collected within the secure University of Wollongong Qualtrics survey platform and stored separately from other study data. An independent research officer will assign each participant a unique study code to enable matching of deidentified data across time points. The linkage file containing names, emails, and study codes will be stored separately from all study datasets and will be accessible only to the independent research officer. Once the linkage process is complete, only deidentified datasets will be stored in the University of Wollongong Microsoft Teams environment, consistent with institutional data governance policies. For the interviews, the interviewer will have access to participants’ names and email addresses for scheduling and conducting interviews. Audio recordings and transcripts will be stored securely in the Microsoft Teams environment, consistent with institutional data governance policies. The research officer will deidentify transcripts and assign interview codes. These codes will be independent of those used for the quantitative data. Only deidentified data will be used for analysis.

